## Abstract

**Background:**

The rate and prevalence of lumbar fusion surgeries are rapidly increasing, and these procedures effectively treat spinal disorders. Biological, psychological, and social factors play important roles in postoperative rehabilitation. Robotic-assisted surgeries reduce postoperative morbidities, and postoperative outcomes can be improved by interventions targeting biopsychosocial factors along with rehabilitation. Hence, this study aimed to determine the effect of biopsychosocial model of rehabilitation on pain in patients after robotic-assisted lumbar fusion surgery.

**Methods:**

An assessor-blinded randomized controlled trial will recruit 136 participants, and randomly allocate the participants into two groups. The intervention group will follow the biopsychosocial rehabilitation model, whereas the control group will be subjected to a routine standard protocol. Assessments will be done at baseline, 2, 4, and 12 weeks post-surgery. The normality of the data will be evaluated using the Shapiro‒Wilk test and analysis of variance with repeated measures or General linear models for intergroup differences. This protocol follows all required ethical guidelines.

**Discussion:**

This study will address the importance of the biological, psychological and sociological factors of rehabilitation. Analysis of the study results will provide insights into the importance of the biopsychosocial rehabilitation model of rehabilitation in patients after lumbar fusion.

**Trial registration:**

CTRI, CTRI/2024/12/077598. Registered on 03 December 2024.

**Supplementary Information:**

The online version contains supplementary material available at 10.1186/s13063-025-09129-6.

## Background

Lumbar fusion is an effective treatment option for a spectrum of spinal disorders, including traumatic, infectious, neoplastic, and degenerative pathologies of the lumbar spine [1]. It is widely used to treat lumbar spinal stenosis, degenerative spondylolisthesis, and isthmic spondylolisthesis [2]. The prevalence of lumbar fusion surgeries is rapidly increasing [3]. Recent studies reported that the rate of spinal fusion has increased by approximately 137% in recent decades [4]. Lumbar spine surgeries are associated with an increased rate of perioperative and postoperative morbidities, such as an extended duration of hospital stay, a need for prolonged rehabilitation, and psychological distress due to preoperative fear, pain, and disability before lumbar fusion surgery [5, 6].

There is a strong influence of pain intensity and psychological factors on variation in mental health, fear of movement/(re)injury, functional disability, and quality of life after lumbar fusion surgery [7]. These factors can negatively influence patient-reported outcomes after lumbar fusion. In recent decades, various surgical techniques have been introduced to minimize morbidities [1] of spine surgeries, such as minimally invasive surgery [8] and robotic-assisted spine surgery [9]. Robotic surgeries have emerged with 99% accuracy in pedicle screw fixation [10] and reduced re-surgery rates by 46% [11] and a fivefold reduction in complication rates [12]. A recent study that compared postoperative outcomes between robotic and open surgery revealed a significant reduction in the length of hospital stay and reduced exposure, but the study was limited in exploring patient outcomes following surgery [13].

The current biomedical model of rehabilitation after lumbar fusion surgery describes the physiological and anatomical causes of a patient’s illness. This approach is limited to considering the environmental, social, and psychological factors that cause patient illness [14]. Biological, psychological, and social factors can influence patients’ outcomes, such as pain intensity, functional activity, and quality of life. The biopsychosocial model of rehabilitation focuses on the integrated framework of patients’ biological, psychological, and social factors that influence disease and illness. Biopsychosocial approaches include behavioral treatment, cognitive behavior therapy, and coping skill training [15].

The biopsychosocial model has a positive impact on musculoskeletal conditions. Research investigating its application in postoperative management has revealed positive effects on catastrophizing pain management and functional outcomes [16]. However, a knowledge gap remains in assessing the impact of rehabilitation following robotic-assisted lumbar fusion. Currently, there is a lack of standardized rehabilitation programs tailored to advanced surgical techniques after lumbar fusion, and there is a paucity of knowledge on the impact of rehabilitation after robotic-assisted lumbar fusion [17]. Hence, this study aimed to determine the effect of biopsychosocial model rehabilitation on pain and function in patients after robotic lumbar fusion surgery.

### Objectives

The study’s primary objective is to find out the effect of biopsychosocial model of rehabilitation after robotic-assisted lumbar fusion surgery on functional disability using Oswestry Disability Index and pain using visual analogue scale.

The secondary objectives are as follows:To examine the effect of biopsychosocial model of rehabilitation after robotic-assisted lumbar fusion surgery on pain catastrophizing using Pain Catastrophizing ScaleTo evaluate the effect of biopsychosocial model of rehabilitation after robotic-assisted lumbar fusion surgery on quality of life using SF-36 questionnaireTo find out the effect of biopsychosocial model of rehabilitation after robotic-assisted lumbar fusion surgery on functional mobility using Timed Up and Go test

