### Outcomes

Baseline assessments will be performed before surgery using the Oswestry Disability Index, visual analog scale, Timed Up and Go test, Pain Catastrophizing Scale, and SF-36 questionnaire. The participants will be reexamined at 2, 4, and 12 weeks after surgery.

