### Sample size

The sample size was calculated using G*Power 3 and based on the Oswestry Disability Index standard deviation and effect size reported by Haoming Wang [26] et al. Study power is considered to obtain a *p*-value of less than 0.05. The power of the study is 0.80. Dropout will be considered up to 15% and calculated using the formula “n/1-dropout rate percentage”. The total number of participants in the study, including dropouts, is 136.

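### ODI and VAS are unranked joint primary outcomes with no decision rule or primary time point, so either the 5% error rate or the 0.80 power, which rests on ODI alone, does not cover the primary objective

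*Protocol article*

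**What the plan says.** - **Objectives.** One primary objective covers both outcomes: the effect "on functional disability using Oswestry Disability Index and pain using visual analogue scale". The Primary outcomes section lists the same two without ranking them.
- **Abstract, Background.** The aim is narrower: to "determine the effect of biopsychosocial model of rehabilitation on pain in patients after robotic-assisted lumbar fusion surgery". The closing sentence of the main Background section gives pain and function.
- **Outcomes.** "The participants will be reexamined at 2, 4, and 12 weeks after surgery". No visit is called primary.
- **Sample size.** The calculation is "based on the Oswestry Disability Index standard deviation and effect size reported by" a cited study, with no number printed. The significance criterion is a p-"value of less than 0.05". "The power of the study is 0.80". No effect size, standard deviation or power is given for VAS. "The total number of participants in the study, including dropouts, is 136".
- **Data analysis.** Group differences are to be assessed by repeated-measures ANOVA or by general linear models. The section names no primary contrast, order of testing, division of alpha or requirement that both outcomes succeed.

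**The concern.** With two primary outcomes of equal rank, a 5% error rate and a power figure mean something only once the rule for a positive trial is fixed. The article gives one alpha and one power for the study as a whole but derives them from one of the two outcomes.

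Two things are at stake. First, if the trial is positive on one outcome and null on the other, the plan offers no agreed reading, and the outcome to emphasise could be chosen after the results are known. Second, the time point is open. A group main effect over all visits, a group-by-time interaction and a week-12 difference answer different questions. The choice matters here because the Interventions section has treatment unsupervised from week 4 to week 12, so the early visits and the last one follow different phases of treatment. The abstract's pain-only aim adds to the ambiguity, since 136 was not derived from pain.

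**Working it through.** **Inputs from the protocol.** Two primary outcomes (Objectives; Primary outcomes). Three post-surgery visits (Outcomes). Alpha 0.05, power 0.80, dropout 15%, total 136 (Sample size). Allocation 1:1 (Assignment of interventions).

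**Assumptions.** Two-sided tests; a two-sample t-test for sizing; VAS with the same standardised difference as ODI; correlation between the two test statistics from 0 to 0.7. The article states none of these.

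**Step 1: the plan's own figure.** 136 cannot be rebuilt forwards, because no ODI effect size or standard deviation is printed. Working back:
- 136 × 0.85 = 115.6 completers, about 58 per arm. As a check, 115 / 0.85 = 135.3, which rounds up to 136.
- A two-sided t-test with 58 per arm, alpha 0.05 and power 0.80 implies a standardised difference d of about 0.525 (0.529 with 57 per arm).

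**Step 2: unadjusted rules, one 0.05 test per outcome.** Under independence:
- Type I error if either suffices: 1 − 0.95² = 0.0975.
- Power to win at least once: 1 − 0.20² = 0.96.
- Power to win on both: 0.80² = 0.64.

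With correlated (bivariate normal) test statistics:

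| Correlation | Type I error, either suffices | Power, at least one | Power, both |
|---|---|---|---|
| 0 | 0.0975 | 0.96 | 0.64 |
| 0.3 | 0.095 | 0.93 | 0.67 |
| 0.5 | 0.091 | 0.91 | 0.69 |
| 0.7 | 0.083 | 0.89 | 0.71 |

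The error column needs no effect size. The power columns need only that each outcome has power 0.80 on its own. If both must succeed, the chance of a false claim stays at or below 5%.

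**Step 3: alpha halved to 0.025 per outcome.** With 58 per arm and d = 0.525, power is 0.71 by the t-test. This hardly depends on d: with 0.80 power at 0.05 the expected test statistic is 1.960 + 0.842 = 2.802, and 2.802 − 2.241 = 0.561 corresponds to a power of 0.71.

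**Step 4: participants needed to restore 0.80 at d = 0.525.**
- Alpha halved: 71 per arm, 142 completers, 142 / 0.85 = 167.1, so 168.
- Both must succeed: 69 per arm (correlation 0.7) to 75 per arm (correlation 0). 138 / 0.85 = 162.4 and 150 / 0.85 = 176.5, so 163 to 177.
- ODI alone, or ODI then VAS in fixed order: 136, with ODI power unchanged at 0.80.

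**Step 5: worst case, not a stated plan.** If both outcomes were tested at all three visits at 0.05, the type I error would be 1 − 0.95⁶ = 0.265 under independence. It would be about 0.18 to 0.23 with a between-outcome correlation of 0.3 to 0.7 and a between-visit correlation of 0.5 to 0.7.

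**The case against.** The strongest reply is that this is a condensed article. The exact contrast and the handling of alpha may stand in a full protocol or analysis plan that is not shown, and sizing on one of two primary outcomes is not in itself a contradiction. The abstract's mention of pain alone may be only a loose phrase, since the Background, Objectives and Primary outcomes sections all cover both pain and function or disability. The power figures also rest on a back-solved effect. A calculation built on repeated measures would imply a different one, and nothing supports equal effects on VAS and ODI.

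Much of this stands, and it limits the point in two ways.

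- **Six tests.** A reader might infer that each outcome will be tested at each visit at 0.05, with an error rate near 20% or above. The document does not say so. The only 0.05 is in the sample-size paragraph, and a repeated-measures ANOVA can give one group or group-by-time test per outcome.
- **Both guarantees lost together.** A reader might infer that neither the 5% nor the 0.80 holds. That merges different rules. If either outcome suffices, error rises but the power to win at least once is 0.89 to 0.96. If both are required, error is kept and only joint power falls. ODI alone at an unsplit 0.05 keeps 0.80.

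The reply does not remove the point. The equal rank of the two outcomes and the single power figure are stated in the article, not left out of it. Which outcome decides the trial, and when, is core protocol content. The error figures do not use the back-solved effect.

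**Conclusion.** The point holds in conditional form. With two equal primaries, the either-suffices rule lifts the type I error to about 8.3% to 9.75%. The both-required rule leaves joint power at about 0.64 to 0.71. Halving alpha leaves about 0.71 per outcome. The last two depend on VAS being as well powered as ODI, which the article does not show. If VAS has less power, joint power is lower. The error range depends only on one 0.05 test per outcome and a correlation between 0 and 0.7. The six-test range of about 18% to 26.5% is a worst case and should not be quoted as the trial's error rate.

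Severity: should-fix. The ODI calculation itself is not shown to be wrong, and a change of wording is enough to settle the matter.

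**What to change.** - Name ODI as the single primary endpoint, at one prespecified time point or contrast. Week 12, the last assessment, is a reasonable choice for the investigators to confirm.
- Test VAS at the same time point second, at 0.05, only if ODI is significant. This order controls the error across the two outcomes at 5% without splitting alpha.
- Label results at the other visits as supportive.
- State in the Sample size section that the 0.80 power applies to ODI only.
- Align the abstract's aim with the objective.

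**Cost.** VAS loses equal primary rank, and the protocol and registry entry need an amendment. Trial status says that recruitment is under way, so this should be done before any unblinded look at the data. No extra participants are needed.

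If the investigators prefer to keep two equal primaries, they should state the decision rule and its power. Restoring 0.80 would then take about 168 participants with alpha halved, or 163 to 177 if both must succeed, under the assumptions above.

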## Methods

### Trial design

This is an assessor-blinded, randomized controlled trial with an interventional and control group.

### Study setting

Participants will be recruited from the Department of Spine Surgery, Manipal Comprehensive Spine Care Center, Manipal Hospitals Bangalore, on the basis of inclusion and exclusion criteria. The eligible and interested subjects attended a baseline assessment before the surgery, and informed consent was obtained from the subjects by the researcher.

### Eligibility criteria

The inclusion criterion for the present study was male and female patients aged 18–65 undergoing index single-level or two-level fusion surgery between the lumbar vertebrae L1 and S1. Eligible participants must be selected for lumbar fusion with decompression and have a primary diagnosis of conditions such as spinal stenosis, spondylosis, degenerative or isthmic spondylolisthesis, or degenerative disc disease.

The exclusion criteria for the study included patients diagnosed with inflammatory conditions such as rheumatoid arthritis and ankylosing spondylitis, as well as those with severe cardiorespiratory issues or neurological deficits classified as ASIA C or above. Individuals with severe psychiatric or psychological disorders, alcohol abuse, or those experiencing immediate postsurgical complications such as infections were also excluded. Additionally, patients with degenerative or idiopathic scoliosis, a history of malignancy in the spine, poor postoperative general health, spinal fractures, worsening existing symptoms, or the emergence of new symptoms will not be considered for participation.

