### Recruitment

Participants will be recruited from the Department of Spine Surgery, Manipal Comprehensive Spine Care Center, Manipal Hospitals Bangalore, on the basis of inclusion and exclusion criteria. The eligible and interested subjects attended a baseline assessment before the surgery, and informed consent was obtained from the subjects by the investigator.

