### Assignment of interventions: allocation

The participants will be randomly allocated into the experimental and control groups using block randomization. Fourteen blocks of block size 10 will be used, and the allocation ratio is 1:1. Concealed allocation will be performed with nontransparent envelopes, which will in turn be signed by the respective supervisor, who is uninvolved in subject recruitment. Once the participant reports, one neutral arbitrator will pick an envelope and provide an intervention to the treating therapist. The study flow is demonstrated in (Fig. 1).

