### Rehabilitation for the control group

The control group rehabilitation interventions (Appendix: II) will focus on treating the physiological and anatomical causes of the patient’s illness, including range of motion exercises, strengthening exercises, and advice for returning to normal activities. The rehabilitation begins with patient education and breathing exercises on POD-1. During POD-2 muscle activation exercise, range of motion exercises for the lower limb and walking with support are performed. The following sessions will consist of returning to normal activity advice, activating and strengthening exercises of muscles, and a demonstration of home exercises. Training intensity progression will be done on the basis of patients’ self-perception of pain.

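### The available text does not rule out applying post-operative and open-ended symptom exclusions after randomisation, so a randomised patient who deteriorates could leave the ODI and VAS comparison

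*Protocol article*

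**What the plan says.** All places are in the protocol article.

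- **Study setting** and **Recruitment** put consent and baseline before the operation: "The eligible and interested subjects attended a baseline assessment before the surgery, and informed consent was obtained from the subjects".
- **Eligibility criteria** excludes on events that exist only after surgery: "those experiencing immediate postsurgical complications such as infections were also excluded". The closing sentence of the section adds, after poor general health following the operation and spinal fractures, "worsening existing symptoms, or the emergence of new symptoms will not be considered for participation". Worsening and new symptoms carry no time window, no threshold and no named assessor.
- **Assignment of interventions: allocation** ties the draw to the patient's arrival: "Once the participant reports, one neutral arbitrator will pick an envelope and provide an intervention to the treating therapist". It does not place that moment before or after surgery, or after a post-operative check.
- **Rehabilitation for the control group** fixes the latest possible time of allocation: "The rehabilitation begins with patient education and breathing exercises on POD-1". **Biopsychosocial model of rehabilitation** likewise starts coping-skill training in the first postoperative session.
- **Withdrawal and drop-out criteria** and **Data analysis** restrict the analysis to patients who finish follow-up. Data analysis also names intention-to-treat, but as a way of handling missing values of patients who drop out.
- **Objectives** and **Primary outcomes** name ODI disability and VAS pain.

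**The concern.** An exclusion harms a randomised comparison only if it can act after allocation. Here three features combine. Some criteria depend on the postoperative course. The symptom criterion has no end date. Allocated treatment begins almost at once after surgery, so any later use of that criterion falls on patients who already have an arm.

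Worsening symptoms are also close to what ODI and VAS measure. Removing a patient on that ground selects on the outcome. If removal differs between arms, the difference in means is biased and harm in one arm becomes less visible. The completers-only rule makes this worse, because a patient taken out of follow-up is also taken out of the analysis. It is not clear that intention-to-treat, as described, covers a patient ruled ineligible rather than one who drops out.

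**Working it through.** **1. Order of events, from the text**

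| Step | Timing given |
|---|---|
| Consent and baseline | before surgery |
| Infection or other immediate complication; poor postoperative health | knowable only after surgery |
| Worsening or new symptoms | no time given |
| Envelope drawn | when the patient reports; not placed relative to surgery |
| First allocated session | first postoperative day |
| Outcomes | 2, 4 and 12 weeks after surgery |

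Allocation is therefore no later than the first postoperative session. A criterion without an end date can still be met after that point, and no sentence says that it then stops applying.

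**2. The plan's own sample size**

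Inputs from Sample size: total 136, drop-out 15%, inflation n/(1 − d), power 0.80, significance level 0.05 (two-sided assumed). The ODI effect size and SD are not printed, so the base number cannot be derived.

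- 115/0.85 = 135.3, rounded up to 136. Per arm, 58/0.85 = 68.2, and 2 × 68 = 136. The drop-out step is sound and implies about 58 evaluable patients per arm.
- Implied standardised effect: (1.960 + 0.842) × √(2/58) = 0.52 SD.

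**3. Illustration of bias (removal rates assumed, not in the document)**

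Assume no true effect, a normal outcome with unit SD, and removal of the worst-scoring fraction p of an arm. With c the upper p point of the normal distribution:

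- mean shift = −φ(c)/(1 − p)
- remaining variance = 1 − cλ − λ², where λ = φ(c)/(1 − p)

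For p = 5%: shift −0.1031/0.95 = −0.109 SD, variance 0.810. For p = 10%: shift −0.1755/0.90 = −0.195 SD, variance 0.712.

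Spurious difference: 0.195 − 0.109 = 0.086 SD. That is 0.086/0.52, about one sixth of the implied effect. At an assumed ODI SD of 15 it is 0.086 × 15 = 1.3 points.

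Standard error with 68 per arm before removal: √(0.810/64.6 + 0.712/61.2) = 0.155. The shift is 0.086/0.155 = 0.56 standard errors, giving two-sided rejection of 8.6%. With 58 per arm the standard error is 0.168, the shift 0.51, and rejection 8.1%.

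| Removed, arm 1 / arm 2 | Bias (SD) | False-positive rate, 58 to 68 per arm |
|---|---|---|
| 5% / 5% | 0 | 5% |
| 5% / 10% | 0.09 | 8.1% to 8.6% |
| 5% / 15% | 0.17 | 17% to 19% |
| 0% / 10% | 0.20 | 20% to 22% |

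**4. Power**

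If removals come on top of the planned 15% drop-out, power at 0.52 SD falls from 80% to 78%, 76% and 73% when 5%, 10% and 15% of the 58 per arm are removed.

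**The case against.** The strongest reply is that these are entry rules. They stand under Eligibility criteria and concern who is considered for participation. Withdrawal has its own section, which does not list worsening or new symptoms as a ground for staff to remove anyone. A coherent sequence is available: consent and baseline, surgery, eligibility check, envelope, first session. On that reading, excluding immediate complications is ordinary screening, causes no bias between arms and uses none of the drop-out allowance. The flow chart and time plan, Figures 1 and 2, are not shown and may set out exactly this order.

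Much of this stands. The text is compatible with screening before randomisation, and a reader should not infer that the plan intends to remove randomised patients for bad outcomes; no sentence says so. Three related inferences also go too far:

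- That worsening and new symptoms are post-operative by definition. They are not labelled so, and they share a list with conditions that can be present before surgery.
- That staff who know the arm apply the criteria. The treating therapist learns the allocation, but nobody is named as applying the exclusions.
- That bias of a given size is to be expected. The removal rates and the SD of 15 are assumptions, and 1.3 ODI points lies below the minimum important difference of 4 to 10.5 points that the article cites.

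The reply does not supply a cut-off. An open-ended criterion sits beside treatment that starts by the first postoperative day, and the available text does not close it at allocation. The conflict between completers-only and intention-to-treat is a separate defect, but it is the route by which a removed patient would leave the comparison.

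**Conclusion.** The point holds as a badly fixed criterion, not as a demonstrated bias. The available text does not rule out applying the exclusions after randomisation, and with the completers-only rule a randomised patient who deteriorates could then be lost from the ODI and VAS comparison.

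The size of any effect is unknown. It is zero if removal is alike in both arms and there is no treatment effect, and it grows with the imbalance between them; the figures above rest on normality, removal of the worst scores and invented rates.

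The ambiguity should be closed, but it is not critical on the text alone. It would become so if any patient has already been removed on these grounds after allocation. That needs checking, because Trial status reports that recruitment began on 15 December 2024.

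**What to change.** Amend Eligibility criteria and the allocation section to state that:

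- the exclusions, including worsening and new symptoms, are assessed once, before the envelope is opened, and cease to apply at that moment;
- complications, worsening or new symptoms arising later are recorded as adverse events and outcomes, not as grounds for exclusion;
- every randomised patient stays in follow-up and in the primary analysis, with the completers-only sentences in Withdrawal and drop-out criteria and Data analysis brought into line;
- patients consented but not randomised are counted and reported separately.

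Check the screening and withdrawal records to date. Where a patient was removed after allocation on these grounds, restore whatever data exist to the analysis and report the case. If Figure 1 or 2 already shows the eligibility check before the envelope, the text should say the same.

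The cost is a short amendment and an instruction to the site. Some consented patients will never be randomised, so somewhat more must be approached to reach 136.
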